## Abstract

**Background:**

People with multimorbidity have complex health care needs, resulting in high health service use, hospital readmission rates, and support needs. To prevent unnecessary hospital readmissions, effective coordination during the transition from hospital to primary care is essential; the transitional care model (TCM) is an effective approach to achieve this. This study will adapt the TCM, focusing on a nurse-led telehealth-based follow-up transition coordination service to enhance continuity between hospital and primary care, aiming to reduce unnecessary hospital readmissions and improve patient transitions.

**Objective:**

This study aims to assess the impact of a TCM on 3-month readmission rates in people with multimorbidity after discharge in an Australian context. Other objectives include evaluating the rate of re-presentation to hospital and overall length of hospital stay within 1, 6, and 12 months of discharge from the index admission; conducting a cost analysis of the transitional service model of care; evaluating the patient experience with the transition service; assessing patients’ symptom burden before and after transitional support service intervention; and evaluating patients’ quality of life, self-efficacy, and symptom management before and after intervention.

**Methods:**

The study design is a multicenter, pragmatic randomized controlled trial of patients with multimorbidity; therefore, real-world clinical practices, and operations will be the considerations within the research design elements. A mixed methods approach using quantitative and qualitative data collection methods will be used. The study setting incorporates 2 hospitals, initially commencing at the Queen Elizabeth Hospital (a 355-bed acute and subacute teaching hospital) and then at the Royal Adelaide Hospital (an 880-bed acute care teaching hospital), both located within the Central Adelaide Local Health Network, South Australia. We will include 3 to 6 medical units and wards. The intervention will focus on nurse-led transition assessment and care planning and telehealth transition coordination support for people with multimorbidity for 6 to 10 weeks following hospital discharge.

**Results:**

This project received ethics approval (17554) on June 29, 2023, and was registered with the Australian New Zealand Clinical Trials Registry on February 15, 2024 (12624000142538). The study commenced on July 1, 2023; data collection started in February 2024 and was completed on March 31, 2025. Finalized results are expected in March 2026.

**Conclusions:**

The Central Adelaide Local Health Network currently lacks a process to assess or manage readmission risks for people with multimorbidity, despite evidence linking transitional care to reduced rehospitalizations. Our feasibility study highlighted the effectiveness of a transition coordinator role in supporting patients’ return to home and community. Progressing this work, an adapted TCM, with telehealth-based follow-up and home and health care support, will enhance continuity between hospital and primary care, aiming to reduce unnecessary readmissions and improve patient transitions.

**Trial Registration:**

Australian New Zealand Clinical Trials Registry (ANZCTR) ACTRN12624000142538; https://www.anzctr.org.au/Trial/Registration/TrialReview.aspx?id=383721

**International Registered Report Identifier (IRRID):**

DERR1-10.2196/71847

## Introduction

### Background

Multimorbidity, the presence of 2 or more chronic conditions, is common and becomes more common with increasing age [1]. It is estimated that 8% of Australians (9.7 million people) had 2 or more chronic disease conditions in 2022. This ranged from 11% of people aged between 0 and 14 years to 79% of people aged ≥85 years [2]. Due to increasing life expectancy and improvements in health care, the prevalence of multimorbidity is rising [3,4]. People with multimorbidity have health outcomes characterized by functional decline, decreased quality of life, and increased mortality [5]. Multimorbidity is also costly for health systems and society due to associations with high patient readmission rates [1], high health care use [6,7], and decreased productivity [8-10]. Historically, the health system has been underpinned and strengthened by the primacy of the single disease model of illness [4,11]. However, there is consensus that the single disease model is unsuitable for people with multimorbidity; a coordinated model of transitional care at the primary and secondary health care interface is required to reduce health service use, hospital readmission, and care fragmentation and support positive patient experiences [4,12].

Several transition interventions have been trialed to reduce high short-term readmission rates [13,14]; however, no discrete intervention or bundle of interventions has been found to reliably reduce rehospitalization. Beneficial interventions for patients with multimorbidity include transition coaches, home visits, and postdischarge telephone calls. However, these patients also often take multiple medications (polypharmacy) and are frequently readmitted due to medication-related issues [15,16]. Depression and anxiety are also common in this group and can lead to poorer health outcomes [17,18]. To address these challenges, interventions such as home medication reviews and mental health care plans may improve overall care for patients with multimorbidity. Nonetheless, services required by people with multimorbidity go beyond their needs in relation to polypharmacy management. Services need to support continuity of care, including multifaceted, time-limited transitional care and multiple health and social service supports and coordination [19,20].

Many services that were previously only provided face-to-face or through outpatient services have successfully, after the COVID-19 pandemic, transitioned to a telehealth service [21]. Still, issues with telehealth delivery persist, including device and internet capabilities at the end of the consumer, the unfamiliarity of the user interface, and uncertainty regarding the cost-effectiveness at the end of the provider [21,22].

Although intensive interventions, including multidisciplinary care and home visits, have been shown to reduce short-term readmissions, they may not be cost-effective in all settings and are difficult to implement across an organization. Low-intensity interventions, such as phone calls, are easy to implement; however, they have not been shown to impact readmission rates by themselves [23]. What is needed is a low-cost intervention that combines multiple interventions into a coordinated package, which can be delivered without requiring face-to-face or outpatient consultations and which, if successful, can be readily spread across an organization.

The transitional care model (TCM) is a nurse-led multidisciplinary model of care developed at the University of Pennsylvania [24]. It focuses on improving the transition of older adults with complex health needs from hospital to home, aiming to reduce hospital readmissions, improve overall patient outcomes, and demonstrate lower overall health care costs by providing comprehensive coordinated care during the critical period following hospital discharge [19,25,26]. Through personalized care coordination, comprehensive assessments (including risk of readmission), ongoing time-limited follow-up, nursing care, and interventions, the TCM has proven effective in enhancing patient care quality while lowering health care costs [26].

To date, there is no evidence that the TCM has been implemented or adapted for implementation within the Australian health care system. However, related transitional care interventions have been trialed. An umbrella review by Berthelsen et al [27], which synthesized findings from 59 randomized controlled trials and 3 quasi-experimental studies relating to key components of the TCM, included 5 systematic reviews conducted in Australia. In these reviews, 5 Australian studies were identified. However, these studies were not direct implementations of the TCM.

The Australian studies included the following: (1) evaluations of general practitioner (GP) involvement in discharge planning to reduce emergency service use [28,29]; (2) a care coordination intervention not based on the TCM [30]; (3) several occupational therapy–focused interventions [31]; and (4) a study related to residential care management [32]. Berthelsen et al [27] also refer to broader evidence regarding GP engagement in transitional care, citing studies such as Allen et al [33], Manderson et al [34], Morkisch et al [19], and Parker et al [35].

In addition, Australia has implemented various care coordination programs, such as Planned Care for Better Health [36] and the inTouch Residential Aged Care Facility Pathway [37], although these initiatives are not based on the TCM. Other programs related to hospital discharge, such as those reported by Courtney et al [38], also diverge from the TCM framework.

A recent feasibility study examined a nurse-led transition care coordinator role designed to improve the quality of transitional care for individuals with multimorbidity at risk of hospital readmission [39]. The study was successful, providing evidence of the role’s acceptability, feasibility, fidelity, and sustainability from both patients and staff in the Australian context. Results highlighted a gap in local health service provision, whereby there was no current process for assessing or managing the risk of readmission for people with multimorbidity, despite international evidence linking effective transitional care to reduced rehospitalization rates [39]. In addition, the study showed that the participants demonstrated significant support needs during the transition period, suggesting that a crucial shift is needed from traditional discharge planning to more tailored transition planning and care coordination for people with multimorbidity [39].

Australia does not have the TCM embedded within its acute care services. This is significant because transition coordination between the primary and secondary health care sectors has been shown to decrease hospital readmissions and increase primary health care use [40]. This study is being implemented at 2 acute hospital sites, both located within the Central Adelaide Local Health Network (CALHN), South Australia; the purpose of the study is to implement an adapted nurse-led TCM to minimize unnecessary hospital readmissions and emergency department presentations for people with multimorbidity [12].

### Aim and Objectives

The aim of this study is to develop and test an adapted nurse-led transition model of care to optimally support people living with multimorbidity after hospital discharge via telehealth and ensure continuity of care between the secondary (acute) and primary health care sectors to minimize direct contact with hospital services.

The objectives of this study are as follows:

To implement an adapted nurse-led TCM interventionTo assess the intervention’s impact on the rate of re-presentation to the hospital (emergency department or hospital admission) within 3 months of discharge from the index admissionTo quantify the rate of re-presentation to hospital (emergency department or hospital admission) within 1, 6, and 12 months of discharge from the index admissionTo calculate a cost analysis of the transition service model of careTo evaluate the participants’ symptom burden, self-efficacy, quality of life, and experience of continuity of care in relation to the intervention

### Hypothesis

We hypothesize that the provision of a nurse-led transition support service (after hospital discharge) for patients with multimorbidity will decrease the short-term hospital readmission rate for this patient cohort.

## Methods

### Ethical Considerations

This project received ethics approval on June 29, 2023, from the CALHN Human Research Ethics Committee (17554). It was registered with the Australian New Zealand Clinical Trials Registry on February 15, 2024 (12624000142538). Written informed consent will be obtained from all participants to ensure that they understand the study requirements, risks, and benefits. If potential participants accept an invitation to participate in the study, they will be provided with a participant information sheet and consent form for consideration. They will then be approached 24 hours later to confirm their willingness to participate. The study commenced on July 1, 2023; data collection started in February 2024 and was completed on March 31, 2025. Finalized results are expected in March 2026.

### Design and Setting

This study is a multicenter pragmatic randomized controlled trial (pRCT) of patients with multimorbidity for deployment at 2 acute hospital sites, initially commencing at The Queen Elizabeth Hospital (a 355-bed acute and subacute teaching hospital) and then at The Royal Adelaide Hospital (an 880-bed acute care teaching hospital), both located within the CALHN, South Australia. Between 3 and 6 medical units or wards will be included per site. This pRCT uses a mixed methods (quantitative and qualitative data collection) approach.

### Data Collection

The pRCT will use a mixed methods approach to data collection, primarily quantitative with a qualitative descriptive component. Data will be gathered through validated patient assessment and transition instruments (Table 1), electronic medical record reviews, phone call support and monitoring, and interviews.

**Table 1 table1:** Data collection instruments, characteristics, and analysis methods.

Instrument	Number of items and response options	Analysis method
Community Assessment Risk Screen [41,42]	Three items (ranging 0-9): 0-3 (low risk); 4-9 (high risk)	Quantitative
Customized transition nursing assessment [43]	A total of 28 summary items	Quantitative and qualitative: open-ended narrative comments from participants
EQ-5D-3L health questionnaire [44]	Five dimensions: mobility, self-care, usual activities, pain or discomfort, and anxiety or depression and patient’s self-rated health on a vertical visual analog scale	Quantitative and qualitative: open-ended narrative comments from participants
Patient Continuity of Care Questionnaire (short) [45]	A total of 12 items	Quantitative and qualitative: open-ended narrative comments from participants
Barthel Index [46]	A scale describing 10 tasks scored according to the amount of time or assistance required by the patient; total score from 0 to 100, with lower scores representing greater nursing dependency	Quantitative
Edmonton Frailty Scale [47,48]	A scale sampling 10 domains, where the maximum score is 17, representing the highest level of frailty	Quantitative
Kessler Psychological Distress Scale [49]	A 10-Item measure designed to assess nonspecific psychological distress	Quantitative
Malnutrition Universal Screening Tool [50]	Three independent criteria are assessed: BMI score, weight loss score, and acute disease effect score; all scores are added, where 0 indicates low risk, 1 indicates medium risk, and a score of 2≥ indicates high risk	Quantitative
General Self-Efficacy Scale [51]	A 10-item scale for a self-rated measurement of self-efficacy; total score between 10 and 40, with higher scores indicating higher self-efficacy	Quantitative and qualitative: open-ended narrative comments from participants
Edmonton Symptom Assessment System [52]	Measures symptom burden of chronic disease and has evolved into an 11-point numeric rating scale, ranging from 0 (no symptom) to 10 (worst possible)	Quantitative

As no suitable preexisting tools were available, customized instruments were developed in REDCap (Research Electronic Data Capture; Vanderbilt University) to capture transition assessment data, medical record readmission data, and phone call monitoring data [53]. Table 1 provides an overview of the validated data collection instruments, their key characteristics, and the planned analysis. All 10 instruments will collect quantitative data, with 4 also incorporating qualitative data.

Throughout the study, researchers and Supporting Transitions and Referrals nurses (STARnurses; recruited to support transitions and referrals) will prioritize patient sensitivity, build rapport, and minimize participant burden.

### Qualitative Data Analysis

Thematic analysis, following the methodology by Braun and Clarke [54], will be used to categorize, analyze, and synthesize data from interviews and qualitative survey responses. Up to 15 interviews will be conducted or until thematic saturation is achieved.

Interview tools, including 12 open-ended questions, will be designed, piloted, and validated by us before data collection. All interviews will be audio recorded and transcribed using artificial intelligence transcription software, with transcriptions reviewed and validated by participants. Once finalized, transcripts will be uploaded to NVivo (Lumivero) software for coding and analysis. To protect confidentiality, all personal and identifiable information will be removed, and participants will be assigned pseudonyms (numerical IDs).

Each transcript will be systematically reviewed and coded, followed by an inductive categorization process. To support theme development, transcripts and categorized data will be read multiple times, allowing for the identification of emerging themes within the categories.

### Statistical Analysis

An intention-to-treat approach will be used. Linear regression analyses will be conducted to estimate the effects of the intervention on primary and secondary outcomes. A fixed effects model will be used to account for stratification at the hospital and unit levels. Sensitivity analyses will be performed to assess the robustness of the findings. Table 2 presents the alignment of data analysis with primary and secondary study outcomes.

**Table 2 table2:** Primary and secondary outcomes—measurement and statistical analysis.

Outcome					Data source, measurement, and analysis

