**Primary**					
	The percentage of patients having hospital re-presentation (emergency department presentation with or without hospital admission) within 3 months of discharge from the index admission			Re-presentation data available from the electronic medical record Statistical analysis: comparison of proportions between treatment and control groups and time to re-presentation analysis using the log-rank test with the method of Kaplan-Meier [55]	

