### Randomization

The randomization will occur at the individual level. The participants will be randomized 1:1, with stratification at the ward or unit level to intervention or control, using REDCap, a secure, web-based software platform designed to support data capture for research studies [53].

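### The text and Table 2 give different analyses for the primary outcome, and none is named as the one that decides

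*Protocol article*

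**What the plan says.** The Statistical Analysis section sets one method for all outcomes: "Linear regression analyses will be conducted to estimate the effects of the intervention on primary and secondary outcomes". It adds "A fixed effects model will be used to account for stratification at the hospital and unit levels" and "Sensitivity analyses will be performed to assess the robustness of the findings", then introduces the table: "Table 2 presents the alignment of data analysis with primary and secondary study outcomes".

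Table 2 defines the primary outcome as "The percentage of patients having hospital re-presentation (emergency department presentation with or without hospital admission) within 3 months of discharge from the index admission" and assigns it "comparison of proportions between treatment and control groups and time to re-presentation analysis using the log-rank test with the method of Kaplan-Meier". That row mentions neither regression nor strata. For the secondary outcomes, Table 2 names nonparametric comparisons for re-presentation rates, length of stay, symptom burden (ESAS), self-efficacy (GSE) and continuity of care (PCCQ). It names no test for cost or for EQ-5D-3L quality of life.

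Under Randomization: "The participants will be randomized 1:1, with stratification at the ward or unit level to intervention or control". Under Design and Setting: "Between 3 and 6 medical units or wards will be included per site".

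**The concern.** A trial with one primary outcome needs one analysis that decides it. Here the text and the table that is meant to align analyses with outcomes do not match, and nothing ranks the methods. Sensitivity analyses are promised, but none of the listed methods is labelled as one.

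Three things are at stake.

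- **Effect measure.** A reader cannot tell whether the headline result will be an adjusted difference, a crude difference in proportions or a time-to-event comparison. A log-rank test can respond to re-presentations that are delayed within the 3 months even if the percentage at 3 months is unchanged.
- **Choice after the fact.** Near p = 0.05 the tests can disagree, and the article as written would support presenting any of them as planned.
- **Use of the strata.** Allocation is stratified by ward or unit. If the two Table 2 tests are run without strata and wards differ in risk, their standard errors are too large.

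For the secondary outcomes, linear regression and nonparametric comparison are both assigned to re-presentation rates and cumulative bed-days. These are likely to be skewed with many zeros, so linear regression suits them poorly.

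**Working it through.** **1. Which analysis does the sample size imply?** Inputs are from Table 3: 80% power, α = .05, control rates 35/40/45%, absolute reductions d of 15, 20 or 25 points. The unpooled two-proportion formula, two-sided and without continuity correction, is

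n per group = (z₀.₉₇₅ + z₀.₈₀)² × [p₁(1−p₁) + p₂(1−p₂)] / d², with (1.960 + 0.842)² ≈ 7.849.

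- 40% v 25%: 7.849 × (0.2400 + 0.1875)/0.0225 = 149.1, so 150 (stated 150).
- 40% v 20%: 7.849 × (0.24 + 0.16)/0.04 = 78.5, so 79 (stated 79).
- 45% v 20%: 7.849 × (0.2475 + 0.1600)/0.0625 = 51.2, so 52 (stated 52).

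All nine cells reproduce exactly. The pooled-variance version (for example 82 for 40% v 20%), the continuity-corrected version (91) and the one-sided version (64) do not reproduce the table. Table 3 is therefore sized for a plain comparison of two proportions.

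**2. How different are the methods?** For a 0/1 outcome, the least-squares coefficient for arm is p₁ − p₀, the difference in proportions. With ward fixed effects it becomes a weighted average of the within-ward differences. So the text's linear model and Table 2's comparison of proportions can estimate the same thing on the same scale, one adjusted and one possibly not. The log-rank test compares event times and does not estimate the 3-month percentage difference.

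**3. What does free choice cost?** Simulation set-up: 200 patients (Sample Size section), 1:1 within ward, 40% event rate, exponential times censored at 3 months, two-sided 5% tests. The tests were a pooled z test of proportions, an unstratified log-rank test and least squares with ward fixed effects. Eight wards of 25 is an assumption; 3–6 units at each of 2 sites gives 6–12. The size of the ward differences is also an assumption. With 20,000 null trials, the Monte Carlo standard error near 5% is √(0.05 × 0.95/20,000) = 0.15 points.

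| Ward differences (assumed) | Proportions | Log-rank | Ward-adjusted linear | Any of three |
|---|---|---|---|---|
| None | 5.2% | 5.2% | 5.1% | 5.8–6.0% |
| Log-hazard SD 0.6 | 3.9–4.0% | 3.6–3.9% | 4.8–5.2% | 5.2–5.3% |
| Extreme: log-odds shifts −1.5 to +1.5 | 3.1% | 2.9% | 4.9% | 5.0% |

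Ranges are from repeated runs. Three independent tests would give 1 − 0.95³ = 14.3%. The observed figures are far lower because the test statistics are almost the same, correlating at 0.985 or more under the null.

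**4. What does leaving out the strata cost in power?** For 40% v 20%:

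- No ward differences: about 0.88 unstratified and 0.87 ward-adjusted.
- Ward SD 0.6: about 86–87% unstratified against 88% ward-adjusted.
- Extreme case: 0.81 (proportions) and 0.82 (log-rank) against 0.84.

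**The case against.** The best defence is that the plan is less divided than it looks. The primary outcome is a percentage and Table 3 is sized on proportions. A linear model on a binary outcome is itself a comparison of proportions. The ward-adjusted risk difference is thus nearly in the text already, and the list is closer to two analyses than three. This stands, and it makes the repair easy. It does not supply the missing designation: the log-rank test sits in the same primary row, joined by a plain conjunction, with no lower status.

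A reader might also infer that the Table 2 tests ignore the ward strata and so contradict the fixed-effects sentence. The article does not support that. Table 2 is silent on strata; it does not say the tests are unstratified, and the adjustment is stated in the paragraph above it. The loss in step 4 is therefore conditional on the tests being run without strata.

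Nor does the article clearly plan linear regression for event times, since Table 2 gives time to re-presentation to the log-rank test. Nor are all secondary outcomes given nonparametric tests: cost and quality of life have none named.

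Finally, an article may leave detail to a fuller plan. That covers model options, but not two statements in one section that assign different methods to the same outcome.

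**Conclusion.** The point holds as a mismatch between the text and Table 2, with no analysis named as deciding the primary hypothesis. It should be fixed, but it does not threaten the trial's validity.

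A reader might infer serious inflation of the false-positive rate from three competing tests. The figures do not bear that out: about 5.8–6.0% with no ward differences and about 5.2–5.3% with a ward log-hazard SD of 0.6. Tests run without strata under that spread err on the conservative side, at about 3.6–4%, and lose about 1–2 points of power. These figures rest on 8 equal wards, a 40% event rate and assumed ward differences; the article gives only the range of units. The main harm is an effect measure and decision rule left open for the primary outcome.

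**What to change.** - Name one primary analysis: the 3-month risk difference with 95% CI, adjusted for randomisation ward or unit as a fixed effect. Either the linear model already in the text, with robust standard errors, or a binomial GLM with marginal standardisation would serve. Both keep Table 3's effect scale, so Table 3 need not change.
- Label a ward-stratified log-rank test with Kaplan-Meier curves as supportive.
- Limit linear regression to outcomes it suits, not skewed re-presentation counts or bed-days, and state one method for each secondary outcome.
- Rewrite Table 2 to agree with the text. Its length-of-stay row also needs correcting, because it names rates of re-presentation as the quantity compared.

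The cost is wording only, with no new data or patients. Data collection closed on March 31, 2025 and final results are expected in March 2026, so the choice should be recorded and dated before anyone sees results by arm. If they have already been seen, the report should say so.
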